### Sample size

The sample size was calculated based on the primary endpoint of changes in body weight. A systematic review on acupuncture for obesity has shown that acupuncture significantly reduced the body weight with average weight loss (MD = 1.56 kg, 95 % CI = 0.74–2.38) [6]. Therefore, a sample size of 60 should be provided to achieve a significance level of α = 0.05 with a power (1 – β) of 90 % using a two-sample *t* test. The number of subjects increases to 72 when estimated 20 % dropouts are considered.

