## Background

Obesity is an increasingly prevalent chronic condition that is associated with serious morbidity and mortality [1]. According to the statistical data of the Centre for Health Protection, Hong Kong SAR in 2013, 36.6 % of the population aged 18–64 were classified as overweight or obese (body mass index, BMI ≥ 23), including 18.8 % as obese (BMI ≥ 25) among all the population. Excess body weight is the sixth most important risk factor contributing to the overall burden of disease worldwide, such as hypertension, heart disease, hypercholesterolaemia, diabetes mellitus, cerebrovascular disease, gall bladder disease, and some types of cancer [2, 3]. Obesity is becoming a global epidemic and common health problem. The weight control treatments commonly used nowadays include behavioural intervention, dietary intervention and physical activity, which require a higher level of self-discipline and take up to 6 months or longer to achieve significant weight change [4]; surgery like the duodenal–jejunal bypass liner, which may cause surgical complications [5]; and anti-obesity medications.

Currently, most of the Western anti-obesity drugs have adverse effects like oily discharge followed by flatus and faecal incontinence for orlistat [6]; headache, nausea and dizziness for lorcaserin [7] or body weight regaining upon cessation of therapy [8]. More people would like to seek help from Chinese herbal medicine (CHM) and/or acupuncture for body weight control, especially from acupuncture because it is safe and does not involve the intake of drugs [9].

Systematic reviews and randomized controlled trials have shown the beneficial effects of acupuncture, including body acupuncture and auricular acupressure [9, 10]. Acupuncture compared with placebo or lifestyle modification had more effectiveness in lowering body weight, BMI and waist circumference and it had a similar efficacy as the Western anti-obesity drugs with fewer reported adverse effects of insomnia, headache or gastrointestinal reactions [10, 11]. Auricular acupressure has been summarized as having the effect of appetite suppression on overweight patients [12], and its efficacy on weight control is higher when combined with body acupuncture [13].

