### Data processing and analysis

All efficacy and safety analyses will be conducted according to the intention-to-treat (ITT) principle. Missing values will be imputed by the last-observation-carried-forward method. The statistical analysis will be performed using the Statistical Package for the Social Sciences (SPSS) for Windows version 21.0. The statistical significance is defined as two-sided *P* value of < 0.05. Baseline characteristics will be reported as mean (SD). Baseline differences between the groups will be assessed with the use of Student’s *t* test for normally distributed continuous variables and the non-parametric Mann-Whitney *U* test for non-normally distributed variables. For categorical variables, the chi-squared test or Fisher’s exact test will be used. Comparisons between groups will be conducted by using an analysis of covariance (ANCOVA) with baseline as covariate. All items and subscales will be compared between groups every 4 weeks using ANCOVA, with treatment group as a factor in the model and baseline as the covariate. The changes from baseline to endpoint of treatment in scores will be tested with a repeated measures analysis of variance (ANOVA). Within-group differences will be assessed with a paired *t* test for normally distributed data and a Wilcoxon signed-rank test for non-normally distributed data.

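### Enrolling 72 participants covers 16.7% dropout, not the stated 20%: after 20% loss 57 to 58 remain, not the 60 tied to 90% power (a minor error)

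*Protocol article*

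**What the plan says.** The Sample size section of the protocol article bases the calculation on the change in body weight. It takes the planning effect from a systematic review, "average weight loss (MD = 1.56 kg", with a 95% CI of 0.74 to 2.38. It concludes that "a sample size of 60 should be provided" for "a significance level of α = 0.05" and "with a power (1 – β) of 90 % using a two-sample" t test. It then adds the dropout allowance: "The number of subjects increases to 72 when estimated" dropouts of 20% are considered. The Abstract and the Study design section both give 72 as the total enrolled in the two groups, so 60 and 72 are both totals.

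The Data processing and analysis section sets a two-sided 5% level and plans intention-to-treat (ITT) analyses with the last observation carried forward (LOCF). Groups are compared by analysis of covariance (ANCOVA) with baseline as covariate.

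**The concern.** The section links three figures: 60 participants for 90% power, 20% dropout, and 72 enrolled. They do not fit together. The 20% was added to the number wanted at the end, whereas dropout removes 20% of the number at the start. The enrolment figure therefore does not deliver the allowance that the protocol says it contains.

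What is at stake is whether the stated power is accurate under the protocol's own dropout assumption. Anyone who reads the result against a design power of 90% would be using a figure that is slightly too high.

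**Working it through.** **Inputs from the protocol article.** Base size 60 in total, dropout 20%, size after allowance 72 in total, mean difference 1.56 kg, power 90%, two-sample t test (all in Sample size); two-sided 5% level (Data processing and analysis). Equal allocation is assumed: there are two groups and blocks of four, but no ratio is stated.

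**Step 1: reproduce the stated figure.**
- n × (1 + d) = 60 × 1.20 = 72. This matches the article exactly.

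**Step 2: apply the stated dropout to 72.**
- Remaining: 72 × (1 − 0.20) = 57.6, so 57 to 58, which is 2 to 3 short of 60.
- Needed to keep 60: 60 / (1 − 0.20) = 75. Inflating each arm of 30 and rounding up gives 38 per arm, or 76; whole blocks of four also give 76.
- Dropout that 72 can absorb while keeping 60: 1 − 60/72 = 16.7%.

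Steps 1 and 2 use only figures printed in the article.

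**Step 3: size the effect on power (assumption needed).** No SD is stated. The CI of 0.74 to 2.38 describes the precision of a pooled mean difference, not the spread between participants. I therefore back-solve the SD that makes the article's own claim exactly true.
- Power of the two-sample t test comes from the noncentral t distribution with n1 + n2 − 2 degrees of freedom and noncentrality 1.56 / (SD × √(1/n1 + 1/n2)).
- At 30 per arm, 90% power requires a standardised difference of 0.851, so SD = 1.56 / 0.851 = 1.83 kg.

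Holding that SD fixed:

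| Completers | Split | Noncentrality | Power |
|---|---|---|---|
| 60 | 30/30 | 3.30 | 90.0% |
| 58 | 29/29 | 3.24 | 89.0% |
| 57 | 28/29 | 3.21 | 88.4% |

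The loss is 1.0 to 1.6 percentage points.

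**Step 4: how firm is 1.83 kg?** It is the largest SD for which 30 per arm still gives 90%. At 1.80 kg, 29 per arm already gives 90.0%, so any SD from just above 1.80 up to 1.83 kg leads to 30 per arm. With an SD near the lower end, 58 completers would have about 90% power. The range of 88% to 89% is therefore approximate and lies at the less favourable end of what fits the figure of 60.

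**The case against.** The strongest reply is that completers are not the analysed set. The article plans ITT with LOCF and measures every 2 weeks, so a participant who leaves after a post-baseline visit stays in the analysis. The number analysed could approach 72, and at an SD of 1.83 kg the nominal power at 36 per arm is 94.5%. This is a fair description of the planned analysis. It does not rescue the statement, because the protocol chose to make a 20% allowance and its figure does not deliver it. A carried-forward early weight also does not hold the full 8-week information, so the nominal 94.5% cannot be taken as the power achieved.

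A second reply is that ANCOVA on baseline could recover the loss. If baseline weight and weight change correlated at 0.2 to 0.25 (an assumption; the article gives no value), 57 to 58 completers would have about 89.6% to 90.8% power. That shows how small the gap is. The article's power claim, however, is for a t test.

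A third reply is that this is a pilot that already names its small sample as a limitation. That bears on the weight of the point, not on the arithmetic.

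Three stronger readings are tempting, and the documents do not support them:
- *That the base figure of 60 is wrong, or that true power is far below 90%.* The missing SD means that 60 cannot be checked from the article, but a condensed article may leave that input to the full protocol. Much lower power follows only from SDs that the reader supplies.
- *That 1.83 kg is the planning SD.* It is a back-solved value, and nothing in the article says that the sponsor used it.
- *That the source of the 1.56 kg is miscited.* The same reference number appears in the Background for "oily discharge followed by flatus and faecal incontinence for orlistat [6"] and in Sample size for the acupuncture review. The reference list is not shown and one source can support both statements, so this merits at most a query.

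**Conclusion.** The dropout arithmetic is wrong as stated. Enrolling 72 allows for 16.7% dropout; at 20%, 57 to 58 participants complete, and 75 would be needed to keep 60. This rests only on the article's own figures.

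The consequence is minor: about 88% to 89% power among completers in place of 90%. That range assumes equal allocation, a t test on completers, a true difference of 1.56 kg, and an SD equal to the value that gives exactly 90% at 30 per arm. A slightly smaller SD that also leads to 60 would shrink the gap further. The point is worth correcting because a stated design figure is inaccurate and restating it is cheap. It does not show that the trial is materially underpowered.

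**What to change.** Keep the enrolment target of 72 and replace the dropout sentence in the Sample size section with wording such as: *72 randomised participants allow for 16.7% dropout with 60 completers; at 20% dropout 57 to 58 complete and power is slightly below 90% (about 88% to 89%).* The sponsor should compute that last figure with its own planning SD, not with the back-solved value used here.

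The change costs one sentence and a slightly less favourable stated power. It needs no extra participants and no change to the analysis.

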### Data processing and analysis

All efficacy and safety analyses will be conducted according to the intention-to-treat (ITT) principle. Missing values will be imputed by the last-observation-carried-forward method. The statistical analysis will be performed using the Statistical Package for the Social Sciences (SPSS) for Windows version 21.0. The statistical significance is defined as two-sided *P* value of < 0.05. Baseline characteristics will be reported as mean (SD). Baseline differences between the groups will be assessed with the use of Student’s *t* test for normally distributed continuous variables and the non-parametric Mann-Whitney *U* test for non-normally distributed variables. For categorical variables, the chi-squared test or Fisher’s exact test will be used. Comparisons between groups will be conducted by using an analysis of covariance (ANCOVA) with baseline as covariate. All items and subscales will be compared between groups every 4 weeks using ANCOVA, with treatment group as a factor in the model and baseline as the covariate. The changes from baseline to endpoint of treatment in scores will be tested with a repeated measures analysis of variance (ANOVA). Within-group differences will be assessed with a paired *t* test for normally distributed data and a Wilcoxon signed-rank test for non-normally distributed data.

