### Objective

The aim of the study is to assess the efficacy and safety of body acupuncture and auricular acupressure compared to sham acupuncture on body weight control through a pilot randomized controlled study.

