#### Sham acupuncture

For subjects assigned to the control group, Streitberger’s non-invasive acupuncture needles (Gauge 8 × 1.2”/0.30 × 30 mm) will be applied to serve as a sham control at the same acupoints with the same stimulation modality, except that the needles are only adhered to the skin instead of being inserted [16]. The validity and credibility of this system has been well demonstrated [17, 18].

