### Outcome measures

The primary outcome is the change in body weight before and after treatment. The secondary outcomes include changes in BMI, waist circumference, hip circumference and body fat percentage during the treatment and follow-up period. Besides at baseline (0 week), the numbers will be measured every 2 weeks. Both the body weight and body fat percentage will be measured with the Omron Karada Scan HBF-701.

Adverse events will be noted throughout the study, based on participant reports and laboratory tests (whole blood counts, renal and liver functions) if needed. All clinical adverse events will be recorded according to terms of intensity (mild, moderate or severe), duration, outcome and relationship to the study.

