### Randomization assignment

Subjects of both groups will be randomly assigned to receive acupuncture (body and auricular acupressure) or control (sham) treatment. For randomization, simple, complete non-sequential random numbers will be generated in advance by a computer program in a block of four, and kept by the principal investigator (PI, [name]). After a patient’s eligibility is confirmed, a randomization number which corresponds to the group allocation will be provided to the acupuncturist by the PI. This arrangement will ensure that the clinical assessor and participants are blinded to the allocation.

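### Safety is placed under intention-to-treat along with efficacy, which can pull the acupuncture–sham harm comparison towards no difference if anyone goes untreated or receives the other arm's treatment

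*Protocol article*

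**What the plan says.** The analysis section of the Protocol article sets one principle for both kinds of outcome: "All efficacy and safety analyses will be conducted according to the intention-to-treat (ITT) principle". No separate safety or as-treated set is defined anywhere in the article.

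Safety is part of the stated purpose. The Objective section reads: "The aim of the study is to assess the efficacy and safety of body acupuncture and auricular acupressure compared to sham acupuncture". Under Outcome measures, "Adverse events will be noted throughout the study, based on participant reports and laboratory tests", the latter where needed.

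The arms differ in physical exposure. Under Body acupuncture treatment, needles go in to a depth of 10–25 mm. Under Sham acupuncture, the control is the same "except that the needles are only adhered to the skin instead of being inserted".

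Randomisation comes after eligibility is confirmed and before treatment. At that point "a randomization number which corresponds to the group allocation will be provided to the acupuncturist by the PI".

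**The concern.** Intention-to-treat is favoured for efficacy partly because deviations from assigned treatment usually dilute the contrast, so a claim of benefit is made harder. For harms, the same dilution makes it easier to conclude that acupuncture is as safe as sham.

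There are two routes:

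1. Someone randomised who never attends a session cannot have a needle-related event, yet counts in the denominator.
2. Someone who receives the other arm's needles has any resulting event counted under the assigned arm.

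The main safety question here is what happens to people who are actually needled, and strict intention-to-treat does not answer it directly. The trial is described as a pilot for a larger one, so its harm rates may be carried forward.

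This is not a complaint that the article leaves something to a fuller document. It states a rule for safety, and the rule is the one at issue.

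**Working it through.** **Inputs**
- Total randomised: 72 (Sample size section), which is 60 × 1.20. It serves here only as a denominator.
- Per arm: 36. This is an assumption, 72 / 2. The article mentions blocks of four but states no ratio.
- Never treated per arm, u: not given. Range shown: 0, 1, 2, 4, and 7 as an extreme. The 7 comes from 20% of 36 = 7.2, as if every expected dropout left before the first session.
- Participants given wholly the other arm's treatment, x in each direction: not given. Range shown: 0, 1, 2.
- Adverse-event risks among the treated: not given. Illustration assumed: 20% acupuncture, 5% sham.
- Never-treated participants are assumed to contribute no events.

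**Route 1: never treated, same number in each arm**

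Intention-to-treat risk = risk among the treated × (36 − u)/36. The risk difference scales by the same factor.

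| u per arm | Factor | Relative dilution | Difference (15.0 points among the treated) |
|---|---|---|---|
| 0 | 36/36 = 1.000 | 0% | 15.0 |
| 1 | 35/36 = 0.972 | 2.8% | 14.6 |
| 2 | 34/36 = 0.944 | 5.6% | 14.2 |
| 4 | 32/36 = 0.889 | 11.1% | 13.3 |
| 7 (extreme) | 29/36 = 0.806 | 19.4% | 12.1 |

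The risk ratio does not change here, because both risks carry the same factor: 20/5 = 4 throughout.

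If non-starters are unequal, direction depends on the arm. With 2 in the acupuncture arm only, the difference is 20 × 34/36 − 5 = 13.9 points. With 2 in the sham arm only, it is 20 − 5 × 34/36 = 15.3 points, slightly away from no difference.

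**Route 2: other arm's treatment received, x each way**

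With pₐ and pₛ the risks under acupuncture and sham, the intention-to-treat difference is [(36 − x)pₐ + x·pₛ]/36 − [(36 − x)pₛ + x·pₐ]/36 = (pₐ − pₛ)(1 − 2x/36).

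- x = 1: factor 1 − 2/36 = 0.944, difference 14.2 points.
- x = 2: factor 1 − 4/36 = 0.889, difference 13.3 points.

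Expected events in the whole trial are unchanged. With x = 1 they are 35 × 0.20 + 1 × 0.05 = 7.05 in the acupuncture arm and 35 × 0.05 + 1 × 0.20 = 1.95 in the sham arm, 9.00 in total. With no swaps they are 36 × 0.25 = 9.00.

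**The case against.** **The two sets may be identical.** The article gives no expected number of non-starters or wrong-needle cases and plans no crossover. This stands, and it is why the effect can only be called possible.

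**Needle errors look unlikely.** The acupuncturist is given the allocation, the sham is a distinct device, and practitioners are trained to a predefined protocol. This stands: nothing in the article suggests such errors are expected. Even if one occurred, the event would still be counted. The contrast would shrink, but total harm would not be hidden.

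**The effect is small against the noise.** Suppose 5 events and 3 non-starters in an arm of 36. The risk moves from 5/33 = 15.2% (exact 95% interval 5.1–31.9%) to 5/36 = 13.9% (4.7–29.5%), a shift of 1.3 points inside intervals about 25 points wide. This stands too, and limits the weight of the point.

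**The expected dropout might seem to measure the bias.** The sample size section says: "The number of subjects increases to 72 when estimated 20 % dropouts are considered". A reader might infer that about a fifth of participants would be wrongly counted as exposed. The document does not support that. The figure covers dropout as a whole, and anyone who leaves after one or more sessions is in both the intention-to-treat set and a treated set. The 19% row above is a ceiling under an extreme assumption, not an expectation. Rates per session delivered are a reporting detail an article may leave out, and their absence is no fault here.

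**Regrouping by treatment received has its own problem.** Moving a mostly sham participant into the acupuncture group because of one stray session would add mainly sham exposure to that denominator and depart from randomisation. This stands, and is the reason to list mixed cases separately.

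None of this makes intention-to-treat the better primary set for harms. The set should be right before it is known whether deviations occur.

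**Conclusion.** The point holds in a conditional form: the stated rule can bias the harm comparison, normally towards no difference. A reader might go further and infer that the plan does understate harm. The article does not show that, because it gives no number of untreated or wrongly treated participants.

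The size is zero if all are treated as randomised. It is about 3% to 11% relative dilution of the event risks and their difference for 1 to 4 never-treated participants in each arm, and about 6% to 11% of the difference for 1 or 2 participants swapped each way. These figures rest on 36 per arm, no events among the untreated, equal numbers affected in both arms, and complete swaps. This is a minor improvement, worth making because it is cheap and safety is a stated aim.

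**What to change.** In the analysis section, limit the intention-to-treat rule to efficacy and add a sentence on safety along these lines: safety will be analysed in all participants who received at least one treatment session, grouped by the treatment actually received; participants who received both penetrating and sham needles will be listed separately; a summary by assigned arm will be given as a check.

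The cost is that sentence and one additional summary table. The downside is that the safety groups may differ slightly from the randomised groups, so the safety comparison is no longer strictly randomised; the assigned-arm summary shows whether that matters. If everyone is treated as randomised, the two summaries coincide and nothing is lost. The Trial status section says recruitment is still under way, so the change can be made before analysis.

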## Methods/design

### Study design

This is a pilot single-blinded, randomized, sham-controlled trial on acupuncture for body weight control conducted at Hong Kong Baptist University Chinese Medicine Clinics. Seventy-two participants will be enrolled from the public through advertisements via the university’s website and newspaper. Subjects will be randomly assigned to the acupuncture group or the control group. Treatment will be given with two sessions per week for 8 weeks, and the post-treatment follow-up period will be 8 weeks. The primary outcome is the change in body weight before and after treatment. The total study period will be 16 weeks. The study protocol has been approved by the Hong Kong Baptist University Ethics Committee on the Use of Human Subjects for Teaching and Research (Approval no. HASC/13-14/0266) and registered in ClinicalTrials.gov (NCT02516878). The flow chart of the trial is shown in Fig. 1. The checklist for items in STRICTA 2010 is given in Table 1. Informed consent is obtained from each participant.

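### Last observation carried forward is the only rule for missing values; it dilutes the week-8 weight difference under equal dropout, can bias it either way under unequal dropout, and assumes no change after the last visit in follow-up

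*Protocol article*

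**What the plan says.** Data processing and analysis gives one rule for missing data: "Missing values will be imputed by the last-observation-carried-forward method". The rule covers all outcomes and both study periods, and no alternative or sensitivity analysis is named. The same section says "All efficacy and safety analyses will be conducted according to the intention-to-treat (ITT) principle", so the filled-in values are what keep people who leave in the comparison.

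Outcome measures defines the endpoint: "The primary outcome is the change in body weight before and after treatment". Study design sets the periods: "Treatment will be given with two sessions per week for 8 weeks, and the post-treatment follow-up period will be 8 weeks". The endpoint is therefore read here as week 8. For later visits, "The secondary outcomes include changes in BMI, waist circumference, hip circumference and body fat percentage during the treatment and follow-up period". On the schedule, "Besides at baseline (0 week), the numbers will be measured every 2 weeks".

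Sample size uses a mean difference of 1.56 kg (95% CI 0.74 to 2.38), asks for 60 participants at 90% power, and enrols 72 to allow for 20% dropout. The between-group analysis is ANCOVA with baseline as covariate, every 4 weeks, alongside a repeated-measures ANOVA.

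**The concern.** Carrying the last value forward assumes that a person's weight stops changing on the day of the last visit. The trial is built on the opposite premise: a difference is expected to develop over 8 weeks of treatment, and measurement continues for 8 weeks after it.

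During treatment, someone who leaves early is held close to baseline. This removes part of the treatment effect, and also part of any loss that both arms share. Shared loss is plausible, because both arms receive the same meal and snack advice (Sham auricular acupressure section). If the arms lose people at different rates, the shared loss is removed unequally and appears as a treatment difference. Unequal dropout cannot be ruled out, because one arm has inserted needles and the other does not.

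During follow-up, someone lost after week 8 is credited with the whole end-of-treatment result at week 16. In both periods the filled-in values are analysed as if observed, so the standard errors ignore the uncertainty of imputation.

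At stake are the size of the primary estimate, its false-positive rate, and what the trial reports about the weeks after treatment.

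**Working it through.** **Inputs from the article.** Difference D = 1.56 kg; 60 participants needed; two-sided alpha 0.05; power 90%; dropout 20%; 72 enrolled; visits every 2 weeks; treatment to week 8 and follow-up to week 16.

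**The plan's own figure.** The 60 cannot be reproduced, because no SD is given. With 30 per arm, a two-sample t test and 90% power, the implied SD is about 1.83 kg. The 72 is 60 × 1.2. The bias calculations need neither figure; only the type I error uses the SD and 36 per arm.

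**Assumptions, not in the article.** Loss is linear over weeks 0 to 8. Dropouts were last seen at week 0, 2, 4 or 6 with equal chance. A dropout then carries on average (0 + 0.25 + 0.50 + 0.75)/4 = 0.375 of the week-8 change, so a fraction 0.625 is missed. With dropout d in an arm whose true mean loss is S, the expected carried-forward loss is S × (1 − 0.625d).

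**Week 8, equal 20% dropout.**
- 1.56 × (1 − 0.625 × 0.2) = 1.56 × 0.875 = 1.365 kg, a 12.5% dilution.
- All dropouts last seen at baseline: 1.56 × 0.80 = 1.25 kg.
- All last seen at week 6: 1.56 × 0.95 = 1.48 kg.
- With no true effect, simulated type I error (36 per arm, SD 1.83, t test on change) stays near 5%.

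**Week 8, no true effect, dropout 10% acupuncture and 30% sham (assumed split).** The false difference is S × 0.625 × (0.3 − 0.1) = 0.125 × S.
- S = 1.5 kg: 0.19 kg, type I error about 7.5%.
- S = 2.5 kg: 0.31 kg, type I error about 11%.
- Check: the standard error is 1.83 × √(2/36) = 0.43 kg, so the shifts are 0.43 and 0.72 standard errors. With the SD held at 1.83, the noncentral t gives 7.1% and 11.0%.

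**Week 8, true effect 1.56 kg, dropout 30% acupuncture and 10% sham.** The retained fractions are 0.8125 and 0.9375.
- Sham loss 0: 1.56 × 0.8125 = 1.27 kg.
- Sham loss 2 kg: 3.56 × 0.8125 − 2 × 0.9375 = 2.8925 − 1.875 = 1.02 kg.

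**Same effect, 10% acupuncture and 30% sham.**
- Sham loss 0: 1.56 × 0.9375 = 1.46 kg.
- Sham loss 2 kg: 3.56 × 0.9375 − 2 × 0.8125 = 3.3375 − 1.625 = 1.71 kg, now above the truth.

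**Week 16.** Let r be the fraction of the week-8 loss regained.
- 20% per arm lost after week 8: the reported difference is 0.8 × (1 − r) × 1.56 + 0.2 × 1.56. For r = 0.5 this is 0.94 kg against a true 0.78. For r = 1 it is 0.31 kg against 0.
- 20% per arm lost during treatment: each carries 0.375 × 1.56 = 0.585 kg. For r = 0 the report is 0.8 × 1.56 + 0.2 × 0.585 = 1.365 kg against 1.56. For r = 0.5 it is 0.8 × 0.78 + 0.117 = 0.74 kg against 0.78. This group understates the difference unless more than 62.5% of it has been regained.
- Losses after week 8 of 10% acupuncture and 30% sham, week-8 losses 2.56 and 1.0 kg, r = 1: 0.1 × 2.56 − 0.3 × 1.0 = −0.04 kg against 0.

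The sign at week 16 thus depends on when people leave, from which arm, and how much is regained.

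**The case against.** The strongest defence is that the method is conservative under the only dropout figure the article gives. With 20% in each arm it shrinks the difference and leaves type I error near 5%. The 10%/30% split is assumed, and nothing in the article predicts it. Even then the false benefit of 0.19 to 0.31 kg is small beside a 95% confidence half-width of about 2 × 0.43 = 0.86 kg. The trial also calls itself a pilot with a small sample. All of this stands and limits severity. It does not make carrying forward safe as the sole method, because the balance of dropout is unknown in advance and the error can favour either arm.

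Three stronger readings are tempting and not supported:
- **That power falls materially.** Lowering the effect to 1.365 kg at a fixed SD of 1.83 suggests a loss. But the SD is only implied, and values frozen early also vary less. When spread is assumed to grow over time, simulated power is about 89.5% to 91%.
- **That follow-up exists to detect regain, or that regain is the chief drawback of current therapy.** Background mentions "body weight regaining upon cessation of therapy" as an alternative to adverse effects, unranked, and no stated aim links follow-up to regain. Body weight is not itself listed for follow-up, although BMI carries the same information at fixed height.
- **That week 16 is always biased toward a maintained benefit.** The calculations show that the direction is conditional.

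**Conclusion.** The concern holds as a should-fix. The article fixes a single imputation rule that contradicts the expected course of the outcome, and offers no check on it. At week 8, equal 20% dropout costs about 0.2 kg of a 1.56 kg difference (range 0.08 to 0.31 kg by timing), without raising type I error. Unequal dropout can move the estimate in either direction and, under the assumed 10%/30% split with shared loss, raise type I error to about 7.5% to 11%.

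In follow-up only secondary outcomes are affected. For people lost after week 8 the rule overstates persistence if regain occurs. People lost during treatment generally pull the other way, so no net direction can be claimed.

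These sizes rest on linear loss, the assumed spread of last visits, the assumed dropout split and shared loss, and, for type I error, the implied SD of 1.83 kg. The 1.56 kg and the 20% are the article's own.

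**What to change.** Replace last observation carried forward as the primary method. Analyse body weight with a likelihood-based repeated-measures model on the scheduled two-weekly measurements, with arm, visit, arm × visit and within-person covariance. Make the week-8 body-weight contrast primary, and treat the follow-up contrasts for BMI, waist, hip and body fat as secondary in the same kind of model.

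A model of post-baseline visits alone would drop anyone last seen at baseline. To keep all randomised participants in, include baseline as an outcome with a mean common to both arms, or use multiple imputation instead.

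Name a fallback covariance structure in advance. If the two-weekly schedule runs to week 16 there are 9 time points, and an unstructured matrix has 9 × 10/2 = 45 parameters for 72 participants.

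Both approaches assume that dropout is explained by observed data. Add one sensitivity analysis that returns dropouts toward baseline or toward the sham trajectory. Last observation carried forward may remain, but only as a further sensitivity analysis.

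The cost is a change of wording and slightly more analysis work. No new data are needed, and the article reports that recruitment is still under way, so the change can be made before analysis.
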